### Outcome measures

The primary outcome measures in our study will be 7-day point prevalent abstinence rate (PAR), continuous abstinence rate (CAR), end-expiratory carbon monoxide levels (CO), nicotine withdrawal symptoms according to the Minnesota Nicotine Withdrawal Scale (MNWS) and stress level according to the Stress Check List (SCL). PAR is defined as abstinence from tobacco smoking for the previous 7 days, whereas CAR is defined as abstinence since the target quit date. The time taken (T) to reach the quit date is also recorded. During the active intervention period (week 2 to week 7), the following will be assessed weekly: number of cigarettes smokes per day, CO, MNWS and SCL. At week 3, 5 and 7, CAR and PAR will be assessed. At week 13 and week 26, successful quitters will be assessed for CO, PAR, SCL and MNWS. At week 2 and week 8/one week after successful quitting, expectancy of treatment will be assessed in all participants with a modified 4-item Borkovec and Nau self-assessment credibility scale as adopted by Tough *et al. *[40] in acupuncture related studies.

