### Statistical analysis

Baseline characteristics of participants (age, number of cigarettes smoked per day, history of packed-years and number of previous cessation attempts) in all the three arms will be expressed as mean values ± standard deviation (SD). The null hypothesis will be adopted in comparing the outcomes (PAR, CAR, CO levels, MNWS score and SCL scores) between Arm 1 and Arm 3, Arm 2 and Arm 3, and finally between Arm 1 and Arm 2. In view of the small sample size for each arm, the Mann-Whitney-Wilcoxon two-sample rank sum test will be used for each Arm pair. Medians will be calculated with the quartiles and the Mann-Whitney *U*. Where possible, treatment effect for each Arm pair comparison will be expressed using the Hodges-Lehmann estimator with the 95% confidence intervals and significance levels.

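### Five co-equal primary outcomes are tested across three arm pairs, with no primary time point, pair or error control, so false-positive risk is inflated and the effect size for planning is undefined

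*Protocol article*

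**What the plan says.** The Outcome measures section gives one list of primary outcomes. It begins "The primary outcome measures in our study will be 7-day point prevalent abstinence rate (PAR), continuous abstinence rate (CAR", goes on to exhaled CO, and ends with withdrawal symptoms and stress, "according to the Minnesota Nicotine Withdrawal Scale (MNWS) and stress level according to the Stress Check List (SCL". No member of the list is ranked above another, and no secondary outcomes are separated from it.

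The same section sets the visits. In weeks 2 to 7, "the following will be assessed weekly: number of cigarettes smokes per day, CO, MNWS and SCL". For abstinence, "At week 3, 5 and 7, CAR and PAR will be assessed". Weeks 13 and 26 cover successful quitters only. No visit is named as the primary one.

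The Statistical analysis section compares all five outcomes "between Arm 1 and Arm 3, Arm 2 and Arm 3, and finally between Arm 1 and Arm 2". It specifies that "the Mann-Whitney-Wilcoxon two-sample rank sum test will be used for each Arm pair", and that effects are reported, where possible, by the "Hodges-Lehmann estimator with the 95% confidence intervals and significance levels". It names no visit for these comparisons, no leading pair, no overall three-arm test and no adjustment, and it does not call the tests exploratory.

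The Background and Study design sections describe a pilot of safety and feasibility that is to supply sample-size and effect-size figures for later trials. The Study aim also asks whether true points bring a benefit over sham points and over no acupressure.

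**The concern.** When five outcomes are all primary and each is tested in three arm pairs, a single nominally significant p-value among many can be presented as a primary result. The nominal 5% no longer describes the risk of error.

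Two things are at stake. The first is the answer to the comparative question in the Study aim. The second is the planning value for the next trial: the protocol wants an effect size but does not say for which outcome, at which visit or between which arms. If that choice is made after seeing the data and follows the most striking result, the effect will tend to be overstated and the next trial underpowered.

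The section on sample size promises suitable statistical methods for foreseeable limitations and points to the Statistical analysis section. That section answers only the small sample size, by choosing a rank test. It does not deal with multiplicity.

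**Working it through.** **Inputs from the protocol article.** Five primary outcomes (PAR, CAR, CO, MNWS, SCL); three arm pairs; 20 participants per arm. All five outcomes are assessed together at weeks 3, 5 and 7. CO, MNWS and SCL have six treatment-period visits (weeks 2 to 7), and PAR and CAR have three.

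**The plan's own figures.** The only one is the total of 3 × 20 = 60, which agrees. No alpha, power or family-wise error rate is stated, so there is none to reproduce.

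**Assumptions.** Two-sided 0.05 per test, in line with the 95% intervals. For the main simulation: between-outcome correlation 0 to 0.7, between-visit correlation 0.5 to 0.8, and true abstinence of 15% or 30% in every arm.

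**Step 1: fewest tests, one visit.** 5 outcomes × 3 pairs = 15 tests. If independent, the chance of at least one false positive is 1 − 0.95^15 = 0.537, or 54%.

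**Step 2: allowing for correlation.** The 15 tests share arms and the outcomes are related, so independence overstates the risk. The null case was simulated with 20 per arm, two binary and three continuous outcomes, and tie-corrected Mann-Whitney tests (1,500 replicates per scenario; Monte Carlo standard error about √(0.45 × 0.55 / 1500) = 0.013). Further simulations at 20 per arm checked the result.

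| One visit, 15 tests | Chance of at least one p < 0.05 |
|---|---|
| Independence formula | 54% |
| Main simulation, either direction | 35% to 47% |
| Second simulation, correlation 0 / 0.3 / 0.6 | 48% / 44% / 37% |
| Third simulation | about 41% to 52% |
| Favouring acupressure (Arm 1 or 2 over 3, or 1 over 2) | about 21% to 30% |

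The either-direction range of 35% to 52% is about seven to ten times the nominal rate (0.35/0.05 = 7; 0.52/0.05 = 10.4).

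**Step 3: visit left open.** If every treatment-period visit were tested, or the visit were chosen after looking at all of them, the count would be (3 outcomes × 6 visits + 2 outcomes × 3 visits) × 3 pairs = 24 × 3 = 72. The simulated chance of at least one p < 0.05 is then 72% to 93% in either direction and 45% to 74% favouring acupressure. This is a ceiling for the treatment period, not what the text prescribes.

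**Step 4: effect of the fix.** One outcome, one visit and one pair gives 5%. One outcome with all three pairs unadjusted gives at most about 1 − 0.95^3 = 14.3%, and 11.8% in simulation with rank tests. Requiring a significant Kruskal-Wallis test first brings this to 4.8%. With exactly three arms the gate is sufficient for that outcome: if all arms are equal, the overall test holds 5%; if one arm differs, only one true null pair remains, and it is tested at 5%.

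**The case against.** The strongest reply is that this is a declared pilot of safety and feasibility, with no confirmatory claim planned. Estimates with confidence intervals are to be given for each pair where possible, not only for significant ones, and nothing says that a chance finding would be carried forward. This lowers the severity. It does not dispose of the point, because the Study aim asks about benefit, significance levels are to be reported, and the effect size wanted for planning is left undefined.

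A reader might infer that every outcome is tested at every visit. Adding the quitter visits would give 72 + 4 outcomes × 2 visits × 3 pairs = 96 tests, and 96 × 0.05 = 4.8 expected false positives. The text does not support this. It says when outcomes are assessed, not when they are tested. The 24 comparisons at weeks 13 and 26 involve successful quitters only, so they would not have 20 per arm, and with very few quitters a rank test cannot reach 5%.

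A reader might also infer that a spurious benefit is likely. At one fixed visit the favourable figure of about 21% to 30% is substantial but below even odds. It reaches 45% to 74% only if all treatment-period visits are tested or searched.

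MNWS and SCL also serve as measures of adverse effects (Adverse events section). With only PAR, CAR and CO at one visit, simulation (correlation 0.3 to 0.8, abstinence 15% to 30%) gives 25% to 30% in either direction and 13% to 17% favourable. That is smaller but still well above 5%.

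Finally, a full protocol or statistical analysis plan may fix the visit or add an adjustment, so the absence of those details alone is no fault. The designation of five primaries and the significance testing of all pairs are stated in this article.

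**Conclusion.** The point holds in a limited form. Five unranked primary outcomes, each tested in three pairs without priority or error control, carry roughly a 35% to 52% chance of at least one false-positive result even at one visit. An unfixed visit adds to that. The figures rest on an assumed two-sided 0.05 and on the assumed correlations and abstinence rates; the protocol gives none of these. The size varies over the assumed range, but the direction does not.

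For a pilot this should be corrected but is not critical. The more practical consequence is that the document does not identify which effect size the later trial is to be built on.

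**What to change.** In Outcome measures and Statistical analysis, name one primary efficacy outcome, one time point assessed in all randomised participants, and one primary arm pair. PAR at week 7, Arm 1 against Arm 2, is an example. Test it at 5%; a single pre-named comparison needs no preliminary overall test. State that this comparison supplies the effect size for the later trial.

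Make all other outcomes, visits and pairs secondary or exploratory, reported as estimates with 95% confidence intervals and without claims of significance.

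If all three pairs are to be tested on the primary outcome, put an overall three-arm test of a type suited to that outcome first. This brings that outcome's error from about 12% to about 5%. It does not control error across several outcomes, so it cannot replace naming one primary. Keeping all 15 tests at one visit under Bonferroni would also hold 5%, but at 0.05/15 = 0.0033 per test, which is severe with 20 per arm.

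The cost is wording in two sections, with no change to sample size or visits. The downside is that fewer results can be called significant.

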**Methods:**

Sixty consenting participants with confirmed habit of tobacco smoking will be recruited and randomized into three arms to receive either auricular acupressure at five true acupoints (NADA protocol), auricular acupressure at five sham points, or no auricular acupressure at all. Participants having auricular acupressure will exert firm pressure to each acupoint bilaterally via the bead in the attached plasters whenever they feel the urge to smoke. The treatment phase will last for six weeks during which all participants will be assessed weekly to review their smoking log, state of abstinence, end-exhalation carbon monoxide levels and possible adverse effects including withdrawal reactions and stress levels. At any time, a successful quit date will be defined with continuous abstinence for the following consecutive 7 days. From then on, participants will be evaluated individually for continuous abstinence rate (CAR), end-exhalation carbon monoxide levels and adverse effects of stress and withdrawal at specified intervals up to 26 weeks. Expectancy of treatment will be assessed with a four-item Borkovec and Nau self-assessment credibility scale during and after intervention.

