### Adverse events and withdrawal from studies

Part of the objectives of our pilot study is to assess the possible adverse effects due either to the auricular acupressure or, due to withdrawal and stress from smoking cessation. The nature and severity of the adverse effects will be recorded and assessed with the MNWS and SCL scores. At any time, participants may withdraw from the study if they develop severe nicotine withdrawal reactions or anxiety symptoms; if they have any adverse effects of pain, discomfort, inflammation or infection at the local sites of the plaster; if there is any inter-current illness that would, in the judgment of the investigators, affect outcome measures to a significant degree; and finally, as requested by the participants.

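### MNWS and SCL are primary outcomes, but their arm contrasts mix any effect of acupressure with the effect of quitting: net symptom burden in weeks 2 to 7, selected quitters afterwards

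*Protocol article*

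**What the plan says.** The Outcome measures section names five primary outcome measures. Beside the two abstinence rates (PAR and CAR) and exhaled carbon monoxide (CO), it lists "nicotine withdrawal symptoms according to the Minnesota Nicotine Withdrawal Scale (MNWS) and stress level according to the Stress Check List (SCL"). The schedule is: "During the active intervention period (week 2 to week 7), the following will be assessed weekly: number of cigarettes smokes per day, CO, MNWS and" (the stress scale closes the list). The Abstract (Methods) adds that "The treatment phase will last for six weeks during which all participants will be assessed weekly", so during treatment the scales are completed by people who have quit and by people who have not. The later visits differ: "At week 13 and week 26, successful quitters will be assessed for CO, PAR, SCL and MNWS".

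The Statistical analysis section treats all five outcomes alike: "The null hypothesis will be adopted in comparing the outcomes (PAR, CAR, CO levels, MNWS score and SCL scores) between Arm 1 and Arm 3", and likewise for the other two pairs. It states that "the Mann-Whitney-Wilcoxon two-sample rank sum test will be used for each Arm pair" and that, where possible, the effect of treatment in each pair is given as a Hodges-Lehmann estimate with a 95% confidence interval. It does not mention smoking status for the two scales, nor which direction of difference is favourable.

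The section on adverse events and withdrawal gives the scales a second role. It sets out to assess adverse effects that come either from acupressure or are "due to withdrawal and stress from smoking cessation", and it grades them with MNWS and SCL. The Abstract also lists withdrawal and stress under adverse effects.

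**The concern.** On the protocol's own account, withdrawal and stress follow from stopping smoking, and stopping smoking is what PAR and CAR count as success. If one arm makes more people quit, more of its members are exposed to the cause of high scores. A higher MNWS or SCL score in Arm 1 could therefore reflect more quitting, a direct ill effect of acupressure, or an absence of relief. A difference near zero could hide a real easing of withdrawal among those who quit.

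This matters because the Background gives the pilot two products: a judgement on safety, and effect sizes for planning later trials. A contrast labelled as a treatment effect on withdrawal or stress feeds both. The weeks 13 and 26 contrasts have a different weakness: who is scored depends on having quit, which the allocated treatment may itself influence, so randomisation no longer makes the groups comparable.

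**Working it through.** **The plan's own figure.** The only numerical design figure is the sample size: 3 arms × 20 = 60, which reproduces. It is a convenience sample. The article gives no effect size, SD or expected score for MNWS or SCL, so the rest is an illustration on assumed inputs.

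**Model, for one visit in weeks 2 to 7.** Scores are in units of the SD within smoking-status groups.
- Continuing smokers average 0 and abstainers average D.
- Abstainers in the better-quitting arm average D − r, where r is any true relief from acupressure.
- p1 and p3 are the proportions abstinent in the two arms.
- Difference in arm means = p1 × (D − r) − p3 × D. A positive value means the better-quitting arm scores worse.
- Relief at which the difference is exactly zero: r* = D × (1 − p3/p1).

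**Inputs.** D is taken from 0.5 to 1.5. Abstinence pairs are kept within the 6% to 50% that the Background cites for other cessation treatments. That range only bounds the illustration; the documents give no expected abstinence for these arms.

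**No true effect on withdrawal (r = 0).** The difference is (p1 − p3) × D.

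| Abstinence | D = 0.5 | D = 1.0 | D = 1.5 |
|---|---|---|---|
| 20% vs 6% | 0.14 × 0.5 = 0.07 | 0.14 | 0.21 |
| 30% vs 10% | 0.20 × 0.5 = 0.10 | 0.20 | 0.30 |
| 50% vs 20% | 0.30 × 0.5 = 0.15 | 0.30 | 0.45 |

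**True relief present.** With 50% vs 20%, D = 1 and r = 0.5, the difference is 0.50 × 0.5 − 0.20 × 1 = +0.05 SD, so the relief is not visible. With 50% in both arms it is 0.50 × 0.5 − 0.50 × 1 = −0.25 SD, so the relief shows, though diluted because only half the arm abstains. The break-even relief is 60% of D at 50% vs 20%, 67% at 30% vs 10%, and 70% at 20% vs 6%.

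**With the planned rank-sum test and Hodges-Lehmann estimate.** There were 4,000 simulated trials per scenario, 20 per arm, normal scores within groups, and two-sided 0.05 assumed.
- 50% vs 20%, D = 1, r = 0: the mean Hodges-Lehmann estimate is +0.30 SD. It is on the wrong side for the better-quitting arm in 79% of trials. The test is significant against that arm in 13% and for it in 0.4%.
- The same with D = 1.5: 89% and 20%.
- 30% vs 10%, D = 1, r = 0: mean estimate +0.20 SD, wrong side in 72%, significant against in 7.5%.
- 50% vs 20%, D = 1, r = 0.5: mean estimate +0.05 SD, significant for the active arm in 1.7%, against 10.7% when both arms have 50% abstinence.

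**Weeks 13 and 26.** No mixture calculation applies, because continuing smokers are not scored. The comparison is between whoever quit in each arm.

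**The case against.** The strongest reply is that the scales are there for tolerability. The protocol never says that MNWS or SCL measures benefit. Where it explains their use, it speaks of adverse effects, and the study aim claims safety, feasibility and help with smoking cessation, not relief of withdrawal. For tolerability, comparing everyone randomised is legitimate: it shows the symptom burden of being assigned to an arm, including burden that comes from quitting more. This stands. A reader might infer that the weeks 2 to 7 contrast is meaningless, or that the protocol declares the scales to be benefit outcomes; the text supports neither.

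The size is also uncertain. No document gives the gap between abstainers and continuing smokers, and it cannot be assumed that those still smoking have little withdrawal. All participants intend to quit, some may be cutting down, and for SCL the sign is less certain still. A significant result in the wrong direction is a minority event: at a 0.20 SD difference and 20 per arm, 0.20 × √(20/2) = 0.63, and the normal tail beyond 1.96 − 0.63 = 1.33 is about 9%. This stands too.

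Finally, PAR, CAR and CO are compared between the same arms, so the abstinence difference will be reported anyway, and presentation detail may sit in a fuller plan. This stands only in part. Separate arm comparisons do not link a participant's score to that participant's smoking status. The primary status of the scales and the description of their contrasts as treatment effects are stated in the article, not left open.

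**Conclusion.** The concern holds in a limited form. The article gives MNWS and SCL two roles, primary outcome and adverse-effect measure, without saying which direction is favourable, and reports their arm contrasts as treatment effects. In weeks 2 to 7 those contrasts validly estimate net symptom burden; reading them as relief by acupressure, or as direct harm from it, is not supported. At weeks 13 and 26 they compare groups selected after randomisation.

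Under the assumed gap of 0.5 to 1.5 SD and abstinence of 50% against 20%, the better-quitting arm scores 0.15 to 0.45 SD worse with no true effect on withdrawal. The distortion is nil if abstinence is equal between arms or abstainers score no higher, and it would reverse if they scored lower. The claim is that this can happen. A reader might infer that a false significant harm is likely or that real relief is bound to disappear; the documents give no figures that would show either. The main risk is to the effect sizes and the safety reading that the pilot is meant to supply.

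**What to change.** In the Outcome measures and Statistical analysis sections:

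1. Make MNWS and SCL secondary outcomes, described as tolerability measures.
2. Keep the comparison of all randomised participants in weeks 2 to 7, state that it is interpreted as net symptom burden, and present it beside the between-arm difference in abstinence.
3. Add a table of scores by arm and smoking status at each visit, using the smoking log and CO readings already planned.
4. Label every comparison restricted to abstainers, including all of weeks 13 and 26, as descriptive, because the group is formed after randomisation.

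The cost is wording and one extra table, with no new visits, measurements or participants. The downside is two fewer primary outcomes, and abstainer tables that will be small: with 20 per arm, 20% abstinence leaves 4 people and 50% leaves 10.

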**Discussion:**

We incorporate validated outcome measures of smoking cessation into our randomised controlled trial design with the objectives to evaluate the feasibility and possible benefits of self-administered auricular acupressure as a non-invasive alternative to pharmacotherapy for smoking cessation.

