### Sample size calculation and randomisation

A convenience sample size of a total of 60 participants will be recruited, with 20 participants per arm after randomisation. Compared to other pilot studies, this sample size is deemed sufficient and appropriate statistical methods will be adopted to accommodate for foreseeable limitations during final analysis (see section on statistical analysis). Randomisation and allocation of subjects will be performed according to the CONSORT standards in terms of randomisation type[37], randomisation generation[38], allocation concealment[39]. All participants will be informed that they will be randomly allocated to one of the three study arms using a computer generated sequence created by the SPSS 11.0 (IBM^© ^SPSS^© ^Statistics, NY, USA). The random allocation will only be disclosed on the date of treatment commencement. Apart from Arm 3 (passive controls with no acupressure), blinding will be ensured in participants of Arm 1 (true acupuncture points) and Arm 2 (sham points). In particular, participants receiving acupressure will be told that the actual points chosen may vary over time to eliminate guessing amongst them during the study. Efforts will also be made to avoid contacts between all participants.

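### PAR, CAR and the quit date carry no CO criterion, although CO is scheduled at the abstinence visits and Arm 3 is unblinded

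*Protocol article*

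**What the plan says.** The section Outcome measures of the protocol article defines the two abstinence outcomes: "PAR is defined as abstinence from tobacco smoking for the previous 7 days", and "CAR is defined as abstinence since the target quit date". The Methods paragraph of the abstract defines the quit date: "a successful quit date will be defined with continuous abstinence for the following consecutive 7 days". None of these mentions CO.

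CO enters as a primary outcome of its own, in a list that runs "continuous abstinence rate (CAR), end-expiratory carbon monoxide levels (CO), nicotine withdrawal symptoms". Statistical analysis then compares PAR, CAR and CO between arm pairs as separate outcomes.

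On timing, Outcome measures states for weeks 2 to 7 that "the following will be assessed weekly: number of cigarettes smokes per day, CO, MNWS and SCL", and that "At week 3, 5 and 7, CAR and PAR will be assessed". At weeks 13 and 26 it lists CO and PAR together, in successful quitters.

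On blinding, the section on sample size and randomisation states: "Apart from Arm 3 (passive controls with no acupressure), blinding will be ensured" in Arms 1 and 2. The Discussion paragraph of the abstract describes the measures this way: "We incorporate validated outcome measures of smoking cessation into our randomised controlled trial design".

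**The concern.** Followed as written, the definitions accept a claim of abstinence without biochemical confirmation, and give no way to settle a conflict with a CO reading from the same visit. Participants in Arm 3 know that they receive no acupressure, and those in Arms 1 and 2 know that they receive some form of it. The tendency to claim abstinence falsely could therefore differ between Arm 3 and the other two. Two of the three planned comparisons are against Arm 3.

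Three features add to what is at stake:

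- With 20 participants per arm, one false claim moves an arm's rate by 1/20 = 5 percentage points.
- The quit date decides who counts as a successful quitter and is assessed at weeks 13 and 26, so an unverified quit date also affects who is followed up.
- The Background says the pilot is meant to supply the sample size and effect size for later trials. A biased abstinence difference would pass into their design.

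**Working it through.** **1. Is CO available when abstinence is judged?**

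| Abstinence assessment | CO scheduled then? | Where stated |
|---|---|---|
| PAR and CAR, weeks 3, 5, 7 | Yes, CO is weekly in weeks 2 to 7 | Outcome measures |
| PAR, weeks 13 and 26 | Yes, same list, successful quitters | Outcome measures |
| CAR after the quit date, up to week 26 | Yes, CO listed beside CAR | Abstract, Methods |

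Outcome measures does not list CAR at weeks 13 and 26; the abstract covers CAR and CO up to 26 weeks.

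**2. What could differential false reporting do?** The article gives no figure to reproduce here. The sample of 60 is a convenience sample (3 × 20 = 60) with no power inputs.

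Inputs from the article: 20 per arm, and a pairwise rank sum test. Assumptions, not in the article: true abstinence t, equal in both arms; the share f of smokers who falsely claim abstinence; a two-sided 5% level.

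Reported rate in an arm = t + (1 − t) × f. With equal t, the false difference between arms A and B is (1 − t) × (f_A − f_B).

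For t = 20% and no false claims in arm B:

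- f_A = 10%: 0.80 × 0.10 = 0.08, or 8 points
- f_A = 20%: 0.80 × 0.20 = 0.16, or 16 points
- f_A = 30%: 0.80 × 0.30 = 0.24, or 24 points

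**3. How often would the planned test reject with no true difference?** Exact binomial enumeration, 20 v 20, one comparison at one visit, rank sum test on the yes/no outcome (tie-corrected, no continuity correction), t = 20%:

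| f in arm A v arm B | Reported rates | False difference | Rejection |
|---|---|---|---|
| 0% v 0% | 20% v 20% | 0 points | 5.0% |
| 10% v 10% | 28% v 28% | 0 points | 5.3% |
| 10% v 0% | 28% v 20% | 8 points | 9.1% |
| 20% v 5% | 36% v 24% | 12 points | 13.6% |
| 20% v 0% | 36% v 20% | 16 points | 20.8% |
| 30% v 0% | 44% v 20% | 24 points | 38.4% |

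For t from 10% to 30%, the unequal cases span false differences of 7 to 27 points and rejection of 7.9% to 54.5%. Equal false reporting of 10% gives no false difference and 5.0% to 5.3%. If a CO criterion removed every false claim, the false difference would be 0 and rejection 3.9% to 5.3%.

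The test is two-sided and the arms are equal in size, so the same figures apply whichever arm over-reports. Over-reporting in Arm 3 would hide a true benefit instead of creating a false one.

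**The case against.** The strongest case on the other side has five parts.

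- **The article does not say how abstinence is ascertained.** A reader might infer that PAR and CAR come from the smoking log alone, that CO is never used to check them, and that someone with a smoking-range CO is counted as abstinent. The documents do not support this as fact. The term self-report is not applied to PAR or CAR, the abstract names the log, abstinence status and CO as separate items of the weekly review, and no passage classifies a discordant case. What stands is narrower: the published definitions contain no CO criterion and no rule for a conflict.
- **An article condenses a fuller protocol.** A cut-off or a missing-reading rule may well sit there. But this article does set out its primary outcome definitions and CO's role as a parallel outcome, so the definitions can be judged as stated.
- **CO is analysed anyway.** A reader might infer that this offers no protection. That goes too far. CO is compared between arms, so a PAR difference with no CO difference would be visible, and at weeks 13 and 26 it is measured in people already classed as quitters, where it bears directly on the claim. Still, the check is indirect: as written it does not change who counts as abstinent.
- **No false-claim rate or direction is documented.** This is correct. Arm 3 also has weekly review with counselling and CO testing, so it may face similar pressure to claim success, and equal false reporting creates no difference where none exists.
- **This is a pilot of safety and feasibility.** No confirmatory claim rests on PAR. That limits the harm, but the aim of informing later trials keeps the abstinence estimate important.

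**Conclusion.** The point holds as a weakness in the stated definitions that is cheap to remedy. PAR, CAR and the quit date rest on abstinence alone, while CO readings that could test each claim are scheduled at the same visits. The exposure is in Arm 1 v 3 and Arm 2 v 3, because Arm 3 is unblinded; Arm 1 v 2 is protected as far as its blinding holds.

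The 8 to 24 points are illustrative. They rest on an assumed 20% true abstinence in both arms and on false claims in one arm only, and should not be read as a forecast of bias in this trial. The conclusion about the definitions depends on none of these values. A reader might also infer that continuous CO has to leave the primary list; nothing in this point requires that.

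**What to change.** Define PAR, CAR and the quit date as reported abstinence plus CO below one cut-off, fixed in advance for the device, at the same visit. For the quit date, use the visit that closes the 7 days. Count a CO reading that contradicts the claim, or a missing reading, as not abstinent. Report abstinence without CO verification as a sensitivity analysis. If CO is already used in this way in the full protocol, say so in the definitions. Continuous CO may stay where it is in the outcome list.

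The cost is mainly wording, because CO is already scheduled at the PAR and CAR visits. One gap needs checking: a 7-day period that ends in week 8 would need a reading then, and Outcome measures lists only the credibility scale at that contact. The downsides are that abstinence rates fall slightly, and that CO covers only recent smoking, so it cannot confirm the full 7 days or the whole CAR period.
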